### Detailed outcome measures collected

#### Duration of shock

The time point at which the patient began in the shock state and the time point at which shock resuscitation was successful during the entire trial process will be recorded, and the shock duration will be calculated.

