**Methods:**

/design.

This single-center, prospective, randomized controlled trial will focus on the efficacy and safety of BRS in early THS resuscitation. A total of 400 adults THS patients will be enrolled in this study. In addition to providing standard care, enrolled patients will be randomized in a 1:1 ratio to receive resuscitation with BRS (test group) or sodium lactate Ringer’s solution (control group) until successful resuscitation from THS. Lactate clearance at different time points (0.5, 1, 1.5, 3, and 6 h) and shock duration after drug administration will be compared between the two groups as primary end points. Secondary end points will compare coagulation function, temperature, acidosis, inflammatory mediator levels, recurrence of shock, complications, medication use, and 7-day mortality between the two groups. Patients will be followed up until discharge or 7 days after discharge.

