#### Blinding

This trial is an open-blinding trial, because patients are usually unconscious and the packaging of the two trial drugs (BRS and LRS) differs significantly.

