### Study procedures

#### Screening procedures

Investigators will use eligibility criteria to identify eligible adults with THS as soon as possible after the patient arrives at the hospital. If the patient meets the criteria for enrollment, the investigator will ask the patient’s legal representative for informed consent to participate in the trial. The screening diary is completed every 2 weeks, and the record investigator will record all patients deemed eligible for the trial. The log will include age, gender, inclusion/exclusion criteria, and other reasons for failure to enter the study arm. The screening log data will be reviewed regularly.

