#### Cessation of study care

For this study, successful shock resuscitation (end of study care) will be defined as the last intravenous injection of BRS /LRS investigator who evaluated the patient’s shock state and believed that shock resuscitation had achieved success.

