#### Sample size

The trial design of this study was a positive drug, parallel-group, and superiority verification. The primary endpoint is the duration of shock and lactic acid clearance rate during the early fluid resuscitation period (6 h). Both primary endpoints were required to be met simultaneously, and Bonferroni correction was used as appropriate. The alpha value = 0.025 (one-sided), power = 0.80 were set. The total sample size was finally determined to be 400 cases with 200 cases in each study arm.

The calculations were as follows:Lactic acid clearance rate: According to a study by Wang et al., the mean value of lactic acid clearance rate after 6 h of fluid resuscitation in the control group was 32% with a standard deviation of 10%, and the expected lactic acid clearance rate after 6 h of fluid resuscitation in the test group was 35% with an equal standard deviation for both study arms [42]. The calculated sample size was 176 cases for each study arm, and a total of 392 cases were required based on 10% of the loss to follow-up.Duration of shock: According to the pre-experimental study, the duration of shock in the control group was 3 h, and in the test group the duration of shock was 1.5 h, with a standard deviation of 4 h. Assuming equal standard deviation for both study arms, the sample size calculated for both study arms was 113 cases, and a total of 252 cases were required based on 10% of the loss to follow-up.

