#### Statistical analysis

This trial was performed using SPSS 26.0 for data analysis. A general linear model was used to correct for selection bias between the two study arms. Categorical data were described as percentages. The measurement data were tested for normality, approximately normal or normally distributed measures were expressed as mean ± standard deviation (x ® ± s), and non-normally distributed measures were expressed as median (quartiles). The chi-square test/ Fisher’s precision probability test was used for categorical data. Paired *t*-test/rank sum test/one-way repeated measures ANOVA/two-way repeated measures ANOVA was used for the measurement data. Kaplan–Meier survival curves were plotted for survival analysis of patients, and differences between the two study arms were compared using the log rank test. Multiple regression analyses were selected to analyze the interrelationships between the factors. The missing data were handled using the last observation carry forward (LOCF) method, and sensitivity analysis was performed using the multiple imputation method. *P* < 0.05 was statistically significant.

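### Duration of shock, a co-primary endpoint, has no value for patients who die in shock, and its start and end are not fixed consistently

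*Protocol article*

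**What the plan says.** - **Role.** Duration of shock and 6 h lactate clearance are the two primary endpoints. Sample size adds: "Both primary endpoints were required to be met simultaneously".
- **Start.** The Duration of shock section records "The time point at which the patient began in the shock state and the time point at which shock resuscitation was successful". The abstract's Methods says "shock duration after drug administration will be compared between the two groups as primary end points". The Sample size section says "The primary endpoint is the duration of shock and lactic acid clearance rate during the early fluid resuscitation period (6 h".
- **End.** Cessation of study care ties success to the last study infusion and to the "investigator who evaluated the patient’s shock state and believed that shock resuscitation had achieved success". Separately, nine clinical criteria (A to I) of successful resuscitation are listed under Initiation of study care. The article does not say whether all or only some must be met, or for how long.
- **Blinding.** "This trial is an open-blinding trial". Under Randomization procedure the investigator opens the envelope at the bedside. Under Test group and Control group, investigators judge shock before each 500 ml administration.
- **Death.** Exclusion criteria include patients who die during the study. Stopping criteria include death within 1 h of intervention. Seven-day mortality is a secondary endpoint.
- **Analysis.** Statistical analysis offers t, rank-sum and ANOVA methods for measurements, and Kaplan–Meier with log-rank for patient survival. "The missing data were handled using the last observation carry forward (LOCF) method", with multiple imputation as a sensitivity analysis.

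**The concern.** The interval closes only at success, so it never closes for a patient who dies in shock. The abstract describes traumatic hemorrhagic shock as having high mortality, so such patients are to be expected. The article's own handling of deaths points to leaving them out after randomisation, which breaks the randomised comparison on an endpoint the efficacy claim depends on. It also sits badly with comparing 7-day mortality.

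The two ends of the interval are loose as well. Different sections imply different clock starts, and staff who know the arm judge the stop. Data collected under these definitions could give several different durations for the same patient.

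**Working it through.** **1. The plan's own figure.** Inputs from Sample size: means 3 h and 1.5 h, SD 4 h, one-sided alpha 0.025, power 0.80, 10% loss. The normal approximation, n = 2(1.96 + 0.84)² × (4/1.5)², gives 112 per arm. The t-based version gives 112.6, so 113. Then 113/0.9 rounds up to 126 per arm, 252 in total. The stated figures reproduce.

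**2. A patient who dies in shock, traced through the plan.**
- The Duration of shock section gives no end time.
- Exclusion criteria, or Stopping criteria if death comes within 1 h, point to removal.
- If the patient is kept and the value is called missing, LOCF has no earlier value of a one-off duration to carry forward.
- Multiple imputation would invent a recovery that did not occur.

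**3. Direction of the bias if deaths are dropped.** Assumptions, none from the article: LRS survival 80%; mean duration 3 h among patients who would survive on either fluid, with no treatment effect on them; BRS saves a further fraction s, whose shock lasts D hours. The BRS survivor mean is (0.80 × 3 + s × D)/(0.80 + s). For s = 0.05 and D = 10 h this is 2.90/0.85 = 3.41 h, a false harm of 0.41 h. False harm in hours over the grid:

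| s | D = 6 h | D = 10 h | D = 24 h |
|---|---|---|---|
| 0.02 | 0.07 | 0.17 | 0.51 |
| 0.05 | 0.18 | 0.41 | 1.24 |
| 0.10 | 0.33 | 0.78 | 2.33 |

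**4. Direction if death were to end the clock.** Assume a fraction d of one arm dies at 1.5 h and would otherwise have averaged 3 h. The arm mean is 3 − 1.5d. For d = 0.10, 0.20 and 0.30 this is 2.85, 2.70 and 2.55 h, so deaths read as short shock. The sign is opposite to step 3.

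**5. Power is not the main harm.** Using the planning values, 200 per arm gives 96% power. Losing an assumed 5 to 30% to death leaves 190 to 140 per arm and 95 to 88%.

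**6. Start.** Shock is an entry criterion (Table 1), so its onset precedes randomisation. For a variable confined to 0–6 h with mean m, the largest possible SD is √(m(6 − m)). That is 3.0 h at m = 3 h and 2.6 h at m = 1.5 h. The planning SD of 4 h therefore cannot belong to a duration bounded by the 6 h period.

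If 4 h is the SD after drug start and the clock begins at onset, an independent pre-randomisation SD of 1, 2 or 4 h (assumed) gives a total SD √(16 + s²) of 4.12, 4.47 or 5.66 h, where s is now that SD. The need becomes 119, 140 or 224 per arm, and power at 200 per arm is 95%, 92% or 76%.

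**7. End.** Shock is judged before each 500 ml. At the stated maximum rate of 10 ml/kg/h, 500 ml takes 500/(10 × weight) hours: 60 min at 50 kg and 33 min at 90 kg (assumed weights). That spacing is 37 to 67% of the 1.5 h effect. Lactate, one of the nine criteria, is scheduled only at 0.5, 1, 1.5, 3 and 6 h and then from 12 h. A patient still in shock when study fluid stops has no end time under Cessation of study care. The urine-output criterion is per hour in Table 1 and per minute in the success criteria; the two must be reconciled.

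**The case against.** How a non-mortality endpoint treats death is often left to the SAP, which is not shown, and Statistical analysis names no test for this endpoint. That stands as far as it goes. The point does not rest on silence, though. The article fixes an endpoint that only success can close, lists death among exclusion and stopping criteria, and names a missing-data method that cannot work for it.

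On the start, the abstract's phrase may only mean that the comparison is made after the drug is given, and the 6 h in Sample size may belong to lactate clearance alone, as in the endpoint list. Pre-randomisation time is also balanced in expectation, so its cost is mainly precision, modest unless its SD approaches 4 h. Both remarks are fair and make this the lesser part. A reader might infer that onset precedes admission for most patients; the article does not say so, only that shock is present at entry.

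On the end, a reader might infer that belief alone stops the clock. The nine criteria, including lactate, heart rate and cardiac output, partly anchor the judgement, and open-label conduct is explained. What remains is the missing all-or-some rule, subjective items such as skin and consciousness, and no named blinded assessor.

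**Conclusion.** The concern holds as an endpoint-definition and bias problem in a co-primary endpoint that must be met. It is not a sample-size error: 113 per arm and 252 in total reproduce.

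That the endpoint has no value for deaths in shock follows from the text alone. The size of the bias does not. Every figure in steps 3 and 4 rests on assumed survival, death times and durations, and should be read as illustration.

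A tempting stronger reading is that early deaths will be counted as the end of shock, so that the plan favours BRS. The documents do not support this. No section lets death end the clock, the exclusion and stopping criteria point to removal, and removal can work against the arm that saves more patients. The inconsistent start and the partly anchored, unblinded end are real but secondary.

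**What to change.** - **Population and origin.** Count from randomisation or first study fluid in all randomised patients. Use pre-randomisation shock time as a baseline covariate if it is recorded. Delete death as a ground for leaving a randomised patient out of the analysis.
- **End.** Reconcile the success criteria with Cessation of study care, and the two urine-output units, into one prespecified rule based on recorded measurements, stating which criteria must hold together. The sponsor must settle the clinical content. Acknowledge that scheduled lactate sampling places resolution within an interval.
- **Analysis.** Treat death before resolution as a competing event (cumulative incidence, Gray's test) and censor unresolved survivors at end of follow-up. Alternatively, rank death worst and unresolved shock next in a rank test. Do not apply LOCF or imputation to deaths.

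**Cost.** Mainly wording, but not free. The article schedules lactate only at fixed times, and its outcome sections give no schedule for cardiac output or mixed venous saturation, so it cannot be assumed that the data for a rule-based end are already collected. The estimate becomes a resolution-rate or rank comparison instead of a mean difference, so the 113-per-arm basis should be restated for the chosen method.

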#### Lactic acid clearance rate of 6 h

The lactic acid in the blood gas results is recorded before fluid resuscitation (0 h) and after resuscitation (0.5, 1, 1.5, 3, and 6 h). The lactic acid clearance rate at the above is calculated based on the time point change in the lactic acid.

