Currently, the most commonly used isotonic crystalloids in clinical treatment are sodium lactate Ringer’s solution (LRS) and sodium acetate Ringer’s solution (ARS), which are distinguished by their fluid components. Lactate and acetate are metabolized in the liver and kidneys to form CO_2_ and H_2_O to maintain acid–base balance and self-clearance. THS patients lose too much blood, resulting in reduced blood perfusion to the liver and kidneys. Additional input of lactate and acetate not only increases the burden on the liver and kidneys but also aggravates the degree of acidosis due to its accumulation, accelerating the process of “bloody vicious circle” making the patient’s prognosis worse. Therefore, use of LRS and ARS is not conducive to patient resuscitation and will affect the efficacy of treatment. Sodium bicarbonate Ringer’s solution (BRS) contains the bicarbonate buffering system and its pH, electrolyte levels, and osmolality are similar to plasma. Studies show that BRS can directly participate in acid–base metabolism, modify base excess (BE) values, maintain acid–base balance, decrease lactate levels, and diminish lung cell apoptosis [32–38]. In contrast, we found that BRS, which is more similar to the plasma component, is expected to be the optimal option. Additional file 1 shows the differences between these fluid components.

At present, there are no large-scale clinical trials of early fluid resuscitation in THS patients using BRS, and systematic and detailed comparisons of the efficacy and safety of these isotonic crystals are lacking. We therefore designed this single-center, prospective, randomized controlled trial.

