**Fig. 3 Fig3:**
[figure not shown]
Drug application process

Clinical criteria of successful shock resuscitation include:(A)SBP was maintaining at 80–90 mmHg(B)Heart rate was less than or equal to 100 bpm/min(C)A pulse of the aorta was palpable(D)Increased cardiac output (greater than or equal to 4.0L/min)(E)Improved peripheral perfusion (ruddy and dry skin, capillary refilling time less than 2 s)(F)Mixed venous oxygen saturation is greater than or equal to 60% and arterial oxygen saturation greater than or equal to 80%(G)The urine volume was greater than that of 0.5 ml/(kg min)(H)Consciousness improvement(I)Lactate level ≤ 2 mmol/L

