##### Control group

For standard care, damage-controlled resuscitation strategy is used, only LRS during fluid resuscitation is used, 500 ml/time is used, dosing rate of ≤ 10 ml/kg/h is used, SBP at 80–90 mmHg is maintained, and the total amount is less than 3L during the resuscitation for the first 6 h. Investigators will evaluate whether the patient’s shock state is corrected before each administration. If the resuscitation is successful, the drug will be stopped, and if the shock persists, the drug will be continued.

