### Outcomes

#### Primary endpoint

(A)Duration of shock(B)Lactic acid clearance rate of 6 h

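### The 6-h lactate clearance endpoint uses raw blood lactate although the control fluid contains lactate, so it can favour BRS without faster shock reversal; duration of shock may lean the same way

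*Protocol article*

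**What the plan says.** The protocol article compares BRS with LRS. Each is the only study fluid of its arm for the first 6 h, with a ceiling below 3 L (Initiation of study care; Test group; Control group).

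- The Background section makes the lactate in LRS part of the rationale: "Additional input of lactate and acetate not only increases the burden on the liver and kidneys but also aggravates the degree of acidosis", because liver and kidney perfusion is reduced in traumatic hemorrhagic shock.
- The primary endpoints are "A)Duration of shock(B)Lactic acid clearance rate of 6 h".
- Lactate is sampled at 0, 0.5, 1, 1.5, 3 and 6 h, and clearance comes from the measured values: "The lactic acid clearance rate at the above is calculated based on the time point change in the lactic acid". Nothing in that section separates infused lactate from the patient's own.
- Duration of shock ends at "the time point at which shock resuscitation was successful". The criteria of success listed under Fig. 3 run from A to I, and the last is "I)Lactate level ≤ 2 mmol/L".
- Cessation of study care makes success the investigator's judgement. The trial is open (Blinding).
- Sample size requires both primary endpoints to be met.

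**The concern.** In the LRS arm, measured lactate is the patient's own plus whatever part of the infused lactate has not yet been metabolised. In the BRS arm it is taken to be the patient's own alone; the composition table is in an additional file that is not shown. By the protocol's own argument the infused part is not negligible in these patients. Clearance can then differ between arms because one bag contains the analyte, with no difference in how fast perfusion and haemodynamics recover.

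The Discussion uses the association of higher 6-h clearance with better prognosis to justify the endpoint, and aims to establish the effectiveness of BRS in resuscitation. That association need not carry over to lactate supplied by the study fluid. A significant clearance result could therefore be real as biochemistry and still not support the stated claim. Because a lactate limit also appears among the success criteria, the second primary endpoint may not be fully independent of the problem.

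**Working it through.** **1. The plan's own figures.** Inputs from Sample size: clearance 32% and 35%, SD 10%; duration 3 h and 1.5 h, SD 4 h; one-sided alpha 0.025, power 0.80, loss 10%.

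n per arm = 2(1.960 + 0.842)²(SD/difference)²

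- Clearance: 175 by the normal formula, 175.4 → 176 by the t distribution. 176/0.9 → 196 per arm, 392 in total.
- Duration: 112 by the normal formula, 112.6 → 113 by the t distribution. 113/0.9 → 126 per arm, 252 in total.

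The stated 176/392 and 113/252 reproduce. With 200 per arm and 10% loss, 180 per arm are evaluable.

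**2. What 3 points means in lactate.** The article gives no formula, so I assume clearance = (L0 − L6)/L0. Then 3 points = 0.03 × L0. Entry requires lactate above 2 mmol/L, but no mean baseline is given. At assumed L0 of 3, 4, 6 and 8 mmol/L the planned effect is 0.09, 0.12, 0.18 and 0.24 mmol/L.

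**3. Chance that a residual alone reaches significance on clearance.** Let r be the mean residual infused lactate at 6 h in the LRS arm, with no true difference. The shift is d = 100r/L0 points, the standard error is 10√(2/180) = 1.054, and the chance is Φ(d/1.054 − 1.960). This takes a constant shift, one common baseline and an unchanged SD.

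| r (mmol/L) | L0 = 3 | L0 = 4 | L0 = 6 | L0 = 8 |
|---|---|---|---|---|
| 0.05 | 0.352 | 0.219 | 0.121 | 0.086 |
| 0.1 | 0.885 | 0.660 | 0.352 | 0.219 |
| 0.2 | >0.999 | 0.997 | 0.885 | 0.660 |

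The nominal rate is 0.025.

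**4. Is such a residual plausible?** r = f × c × V/Vd, where f is the fraction not metabolised, c the lactate content of LRS, V the volume given and Vd the distribution volume. Only the ceiling on V is in the article; the rest is assumed.

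- With c = 28 mmol/L and V = 1.5 to 3 L, the load is 42 to 84 mmol.
- f = 5 to 10%, Vd = 30 to 42 L: r runs from 42 × 0.05/42 = 0.05 to 84 × 0.10/30 = 0.28 mmol/L.
- f = 1 to 2%, same Vd: r runs from 42 × 0.01/42 = 0.01 to 84 × 0.02/30 = 0.06 mmol/L.
- Turned round, the f needed for r = 0.12 mmol/L is 0.12 × Vd/(c × V). It runs from 0.020 (c = 30, V = 3, Vd = 15) to 0.384 (c = 25, V = 0.5, Vd = 40).

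The residual may thus be trivial or larger than the whole planned effect. The article cannot decide which.

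**5. Does lactate decide when shock ends?** Mean 6-h lactate implied by the planning values is L0 × 0.68 (control) and L0 × 0.65 (test):

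| L0 | Control | Test |
|---|---|---|
| 3 | 2.04 | 1.95 |
| 4 | 2.72 | 2.60 |
| 6 | 4.08 | 3.90 |

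At baselines of 4 and 6 mmol/L both arms average above 2 mmol/L at 6 h, yet the planned mean durations are 3 h and 1.5 h. Either lactate is often not the deciding criterion, or most patients start near 3 mmol/L or below. In the latter case the limit falls between the two arm means. The clearance and duration figures come from different sources, so this is an indication only.

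**6. What the both-endpoints rule protects.** For a purely artefactual mean delay in the LRS arm, the standard error is 4√(2/180) = 0.422 h. The chance of significance on duration is 0.025 with no delay, 0.219 with 0.5 h, 0.660 with 1.0 h and 0.945 with 1.5 h. The chance of meeting both endpoints cannot exceed the smaller of the two. With no delay it is at most 0.025, whatever happens to clearance; with 0.5 h it is at most 0.219.

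**The case against.** The strongest reply is that accumulation of infused lactate is the hypothesis. The protocol says it "aggravates the degree of acidosis due to its accumulation", so a fluid that leaves more lactate in the blood is worse, and comparing whole fluids is a legitimate design choice. This stands as far as a biochemical claim goes. It does not show that shock is reversed faster, and raw lactate cannot separate the two.

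A second reply concerns size. Less than 3 L is a ceiling, fluid stops at success, and planned mean duration in controls is 3 h, so many patients may have hours without infusion before the 6-h sample. At 1 to 2% retention the residual is below every planned effect in step 2. This also stands: the size is open.

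Third, 7-day mortality, complications, shock recurrence and vasoactive drug use do not depend on lactate in the same direct way and are already collected. A statistical analysis plan not shown may also hold sensitivity analyses. But the endpoint definitions are fixed in this article, and success rests on the two primaries.

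A reader might go further and infer that both primaries carry the same artefact, that requiring both therefore protects nothing, and that a loop follows from "If the resuscitation is successful, the drug will be stopped, and if the shock persists, the drug will be continued": infused lactate keeps a control patient above the limit, so more LRS is given. The document does not support this as a finding. It lists nine criteria without saying that all must be met, leaves success to the investigator's judgement, and has planning values under which lactate often would not be the last criterion reached.

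**Conclusion.** The point holds for 6-h lactate clearance. The comparator supplies the analyte, the protocol itself says that it accumulates, and the planned effect is small enough (0.09 to 0.18 mmol/L at assumed baselines of 3 to 6 mmol/L) for a modest residual to produce it. A residual of 0.1 mmol/L at a baseline of 3 to 4 mmol/L gives a 66 to 88.5% chance of a significant clearance result with no true difference. These are illustrations. They rest on an assumed clearance formula and baseline, and the real residual depends on fluid composition, retention and distribution that the document does not give.

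For duration of shock, bias in the same direction is possible but its size is unknown. The requirement to meet both endpoints gives reduced protection: strong if lactate rarely decides success, weak if it often does. The sample size is not affected. This should be fixed, with medium confidence, as a cheap improvement that settles what a positive result may claim.

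**What to change.** Leave bedside management and both co-primary definitions as they are. Then:

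1. Prespecify a key sensitivity analysis of duration of shock that uses the listed success criteria other than lactate. Record on the case report form the time at which each criterion is met, from the assessments already made before each administration.
2. State that superiority on 6-h lactate clearance is reported as a biochemical difference, and supports a claim of better resuscitation only if the lactate-free duration analysis agrees. Say beforehand what agreement means.
3. If clearance is described by study-fluid volume, label it exploratory. Volume is determined after randomisation and depends on severity and response, so it cannot isolate the infused lactate.

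Replacing the co-primary itself is not advised: the trial is open and has recruited since May 2021, and the remaining criteria include clinical impressions judged by unblinded staff.

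Cost: a little more data capture and a narrower claim from the lactate endpoint. The article requires an overall judgement of shock before each administration but does not say that single criteria are recorded, so times for patients already enrolled may be only partly recoverable. The 1.5 h planning difference came from the pre-experimental study and may not apply once lactate is left out, so the power of the lactate-free analysis is unknown.
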